**Fig 1 pone.0277369.g002:**
[figure not shown]
Mapping of a hypothetical care pathway in the ED using the Time-Driven Activity-Based Costing.

The decision tree (Objective 3) will be created to reflect the results of the RCT as closely as possible and will therefore include all possible interventions and services used by a participant following the initial visit to the ED for each model of care considered (Fig 2). The pruning of each terminal node containing less than 5% of the participants will be determined based on discussions with a panel of experts. The conditional probability of ending up in each of the remaining terminal nodes of the decision tree will be used to calculate the proportion of disability associated with each care model (Fig 2). The disability proportions obtained for each model of care will be used to determine the number of individuals in each state at entry in the Markov model (Fig 3). The Markov model will then be used to calculate the long-term costs and effectiveness over 2 years of each of the model of care based on the level of disability estimated in the decision tree [35, 37].

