### Data collection

Objectives 1, 2 and 3 will be achieved in part using data collected through a two-arm pilot pragmatic randomized clinical trial (RCT) conducted in the ED of the CHUL, one of the five sites of the CHU de Québec—Université Laval (UL) (Quebec City, Canada) from September 2018 to March 2019 (n = 78). This trial aimed to compare the effects of management by a primary contact physiotherapist to usual care provided by an emergency physician for persons presenting with a minor MSKD on their clinical course (pain and pain interference) and the use of resources at ED discharge and after 1 and 3 months post-visit [29]. Two groups of participants were compared: one group managed by a primary contact physiotherapist and an emergency physician and one group managed by an emergency physician alone.

Data were collected at the initial ED visit and at the one- and three-month post-visit follow-ups. While more details of the data collection procedures can be found in our previous paper [29], any person presenting to the ED who met the inclusion and exclusion criteria was seen by a member of the research team who confirmed eligibility, obtained informed consent, and ensured completion of baseline questionnaires. The participant was then randomized to either study group: primary contact physiotherapist + emergency physician management or usual management by the emergency physician alone. After the ED visit was completed, participants were contacted at 1 and 3 months either by phone or email to complete post-visit follow-ups. The supplementary data needed to meet the three Objectives will come from some of the CHU de Québec—UL administrative databases (nominative data: SIURGE (ED management software), Cristal-Net (patient electronic record), and the CHUL’s ED pharmacy transactions directory; administrative data: prescription and over-the-counter drug costs repository), the scientific literature, and public cost repositories (e.g., salaries of general practitioners and specialists, see https://www.msss.gouv.qc.ca/inc/documents/ministere/acces_info/seance-publique/etude-credits-2018-2019/Reponses-aux-questions-generales-et-particulieres-RAMQ.pdf; laboratory analysis costs, see https://publications.msss.gouv.qc.ca/msss/fichiers/2017/17-922-05W.pdf).

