**Fig 3 pone.0277369.g004:**
[figure not shown]
Projected Markov model covering the period from three to 24 months post initial ED visit.

Both the cost-utility analysis (Objective 2) and the hybrid mathematical model (Objective 3) will be conducted from a Health system and a Societal perspective. Results obtained via the EQ-5D-5L at 1 and 3 months (Objective 2 & 3 –decision tree) will be converted to utility scores using the Canadian conversion algorithm developed by Xie et al. [54]. As the 3-month retention rate for the pilot pragmatic trial was 80% [29], some participants’ data are missing (service and resource use, costs, utility scores). Missing data will be imputed using the Missing not at random (MNAR) multiple imputation method [55]. Patient characteristics believed to have influenced loss to follow-up at 1 and 3 months (e.g., socioeconomic status; level of pain and level of catastrophizing at the ED visit) will be examined to identify if they are indeed predictors of loss to follow-up. Characteristics shown to influence follow-up will be used within multiple imputations and within sensitivity analyses regarding these variables. Uncertainty in cost and effectiveness measures for the cost-utility analysis (Objective 2) will be obtained using non-parametric bootstrap resampling with replacement. Uncertainty in the hybrid model parameters (probabilities, costs, and efficiency) (Objective 3) will be obtained via a probabilistic sensitivity analysis performed using a Monte Carlo simulation. Three scenarios will be considered in the probabilistic sensitivity analyses. The first will assume that all participants with missing follow-up data in the control group will have utility scores at 3 months corresponding to those of the 95th percentile, while all those missing in the intervention group will have scores corresponding to those of the 5th percentile. For the second scenario, we will re-analyze all parameters included in the model, excluding outliers. Finally, in the third and last scenario, the different states of the Markov Model will be based not on the level of pain, but on the level of interference of pain on daily activities. Both uncertainties will be represented visually using a cost-effectiveness diagram, cost-effectiveness acceptability curve, and cost-effectiveness acceptability frontier [35]. As there are significant differences between men and women in the strategies used to cope with pain, and the use of health system services and resources during a painful episode (e.g., [56, 57]), subgroup analyses of men and women will be performed for both objectives (p < .05). Subgroup analyses will also be performed according to MSKD category (spine, upper extremity, and lower extremity) for both objectives (p < .05). All the statistical analyses carried out as part of this project and their detailed reporting in scientific publications will adhere to the CHEERS 2022 standard [58].

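### Markov entry states for the two randomised models are set from per-arm tree proportions without adjustment for baseline pain, which costs some precision and leaves this sample's chance imbalance in the 2-year ICER

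*Protocol article*

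**What the plan says.** Under *Data analysis and interpretation of results*, the article sets out how the tree feeds the Markov model. The first step reads: "The conditional probability of ending up in each of the remaining terminal nodes of the decision tree will be used to calculate the proportion of" (what is meant is disability, separately by care model). The second step reads: "The disability proportions obtained for each model of care will be used to determine the number of individuals in each state at entry". Entry here means the start of the Markov phase at month 3. No covariate is named at either step.

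The same section shows, through its third scenario (states defined by pain interference instead), that the base-case states are defined by level of pain. It also lists characteristics thought to influence loss to follow-up, among them "level of pain and level of catastrophizing at the ED visit". Those found to predict loss go into the multiple imputation and the related sensitivity analyses. None of the three scenarios concerns baseline imbalance.

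Under *Study design and costing approaches*, the tree covers months 0 to 3 and the Markov model months 3 to 24. Under *Study outcomes*, utilities are taken as each participant's difference from baseline. That handles baseline for the trial-period utilities but does not reach the Markov entry states.

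**The concern.** The entry distribution is the link between the randomised data and 21 of the 24 months in the 2-year ICER. It is an arm-level summary of month-3 status from a trial of 78 people. At that size the arms will often differ somewhat in pain at the ED visit by chance. If baseline pain predicts month-3 pain, part of that difference reappears as a difference in entry states and is read as an effect of the care model. The QALY difference in the ICER's denominator may well be small, so modest shifts can matter. The covariate that would deal with this is the baseline value of the variable that defines the states, and it was collected.

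**Working it through.** The article gives no figure to reproduce here.

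**Inputs from the article.** Total 78, two arms (*Data collection*); 3-month retention 80% (*Data analysis and interpretation of results*); Markov phase 24 − 3 = 21 months = 1.75 years (*Study design and costing approaches*).

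**Assumptions.** 1:1 allocation, since the text says only "The participant was then randomized to either study group", giving 78/2 = 39 per arm. Correlation r between baseline and month-3 pain: 0.3 to 0.6. Proportion p in the poor state at month 3: 30-40%. Utility gap between states: 0.1 to 0.3.

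**Size of chance imbalance.** SD of the standardised baseline difference = √(1/39 + 1/39) = 0.226. The probability that it exceeds 0.25 SD in either direction is 27%, and 0.5 SD 2.7%. With about 31 per arm (0.80 × 78 / 2 = 31.2), the SD is 0.254 and the probabilities are 33% and 4.9%.

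**Shift in the entry contrast from a 1-SD imbalance.** Shift = r × 0.226 × φ(z), with φ the normal density at the (1 − p) quantile. SE of the unadjusted difference = √(p(1 − p) × 2/39).

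| p | φ(z) | SE (points) | Shift, r = 0.3 | r = 0.5 | r = 0.6 |
|---|---|---|---|---|---|
| 0.30 | 0.348 | 10.4 | 2.4 | 3.9 | 4.7 |
| 0.40 | 0.386 | 11.1 | 2.6 | 4.4 | 5.2 |

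At p = 0.30, an imbalance at the 1.96-SD limit moves the contrast by 4.6 to 9.3 points.

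**Gain from adjustment (p = 0.30).** Share of variance removed = (shift/SE)²: 5% (r = 0.3), 14% (r = 0.5), 21% (r = 0.6). The SE falls from 10.4 to 10.1, 9.6 and 9.2 points. A simulation of 1,500 trials with a fitted adjusted model gave 3%, 15% and 21%.

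**Effect in QALYs if nobody changes state.** Shift × utility gap × 1.75. Low end at p = 0.30: 0.024 × 0.1 × 1.75 = 0.004. High end: 0.047 × 0.3 × 1.75 = 0.025. At p = 0.40 the high end is 0.052 × 0.3 × 1.75, about 0.028.

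**Effect when states mix.** For a 4-point shift and a utility gap of 0.2:

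| Half-life of the difference | Effective years | QALY |
|---|---|---|
| permanent | 1.76 | 0.014 |
| 12 months | 1.02 | 0.008 |
| 6 months | 0.66 | 0.005 |
| 3 months | 0.36 | 0.003 |

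(The 1.76 arises from counting 46 whole two-week cycles.) For scale, 0.014 QALY equals a utility difference of 0.014/0.25 = 0.056 held through the three trial months.

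**The case against.** The strongest defence is that a condensed article need not list covariates, and the full plan may do so. That carries some weight: the article never calls the proportions unadjusted. But it does more than stay silent. It describes the whole route from node probabilities to entry occupancy, and adding baseline would change that route.

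A reader might infer that the entry proportions are biased. The documents do not support this. Allocation was randomised, so the unadjusted proportions are right on average. Chance imbalance is part of their sampling error, which the planned probabilistic sensitivity analysis carries if entry probabilities are among those sampled. This stands, with one limit: that analysis spreads uncertainty around the observed proportion and does not re-centre it. Recruitment ended in March 2019, so the imbalance is now one fixed, checkable value.

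A reader might also infer that the imbalance acts at full strength for 21 months. That holds only if nobody changes state, whereas the two-week cycles are there to follow clinical change.

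Nor is it right that baseline pain serves only to describe dropout, since it may also enter the imputation and sensitivity analyses. That use is conditional and does not make the arms comparable at entry. The 5% pruning line does not strengthen the point either: it may refer to all 78 participants (3.9 people) and has no bearing on baseline imbalance.

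Finally, replacing the tree with a separate regression would cut the link between care pathways and entry states. This objection stands and shapes the fix. The Discussion acknowledges the small sample, but a caution about interpretation does not recover the lost precision.

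**Conclusion.** The point holds as a modest improvement in method for the two randomised models. As described, entry occupancy takes no account of baseline pain, although pain defines the base-case states and was measured at the ED visit. The consequence is some loss of precision and an uncorrected shift particular to this sample, typically about 2 to 5 points against a standard error of about 10. These sizes rest on 1:1 allocation and on assumed correlation, prevalence and utility gap, none of which the article gives. The QALY range above is a ceiling for a typical imbalance under those assumptions, because it supposes that states persist. Adjustment removes only the part of the imbalance that baseline pain explains. The mechanism does not apply to physiotherapist management alone, whose parameters come from the literature. There the question is whether the source populations are comparable.

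**What to change.** For the two randomised models, standardise the tree's probabilities to the baseline pain distribution of the pooled trial sample, using that one covariate, within the imputed data sets. One way is to weight participants on baseline pain before computing node and disability proportions, so that the tree still links pathways to entry states. Use the results as the Markov entry proportions, base their distributions in the probabilistic sensitivity analysis on the weighted estimates, and report the unadjusted proportions as a scenario. Make this the stated analysis whatever imbalance is observed. In the third scenario, use baseline pain interference if it was recorded; the article does not say so explicitly.

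The cost is some extra analysis and a short addition to *Data analysis and interpretation of results*. For baseline pain no new data are needed. With this sample, adjustment should stay at one covariate. The three-way comparison will then combine two standardised entry distributions with one from the literature that cannot be standardised in the same way, and the report should state this.

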**Fig 2 pone.0277369.g003:**
[figure not shown]
Hypothetical decision tree covering the period from ED visit to three months post initial ED visit.

**Fig 3 pone.0277369.g004:**
[figure not shown]
Projected Markov model covering the period from three to 24 months post initial ED visit.

Both the cost-utility analysis (Objective 2) and the hybrid mathematical model (Objective 3) will be conducted from a Health system and a Societal perspective. Results obtained via the EQ-5D-5L at 1 and 3 months (Objective 2 & 3 –decision tree) will be converted to utility scores using the Canadian conversion algorithm developed by Xie et al. [54]. As the 3-month retention rate for the pilot pragmatic trial was 80% [29], some participants’ data are missing (service and resource use, costs, utility scores). Missing data will be imputed using the Missing not at random (MNAR) multiple imputation method [55]. Patient characteristics believed to have influenced loss to follow-up at 1 and 3 months (e.g., socioeconomic status; level of pain and level of catastrophizing at the ED visit) will be examined to identify if they are indeed predictors of loss to follow-up. Characteristics shown to influence follow-up will be used within multiple imputations and within sensitivity analyses regarding these variables. Uncertainty in cost and effectiveness measures for the cost-utility analysis (Objective 2) will be obtained using non-parametric bootstrap resampling with replacement. Uncertainty in the hybrid model parameters (probabilities, costs, and efficiency) (Objective 3) will be obtained via a probabilistic sensitivity analysis performed using a Monte Carlo simulation. Three scenarios will be considered in the probabilistic sensitivity analyses. The first will assume that all participants with missing follow-up data in the control group will have utility scores at 3 months corresponding to those of the 95th percentile, while all those missing in the intervention group will have scores corresponding to those of the 5th percentile. For the second scenario, we will re-analyze all parameters included in the model, excluding outliers. Finally, in the third and last scenario, the different states of the Markov Model will be based not on the level of pain, but on the level of interference of pain on daily activities. Both uncertainties will be represented visually using a cost-effectiveness diagram, cost-effectiveness acceptability curve, and cost-effectiveness acceptability frontier [35]. As there are significant differences between men and women in the strategies used to cope with pain, and the use of health system services and resources during a painful episode (e.g., [56, 57]), subgroup analyses of men and women will be performed for both objectives (p < .05). Subgroup analyses will also be performed according to MSKD category (spine, upper extremity, and lower extremity) for both objectives (p < .05). All the statistical analyses carried out as part of this project and their detailed reporting in scientific publications will adhere to the CHEERS 2022 standard [58].

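### The main imputation is labelled MNAR, but the steps described are MAR-type, and the stated route for predictors into the model is their link to dropout rather than to costs and utilities

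*Protocol article*

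**What the plan says.** All the relevant text is in the Protocol article, Data analysis and interpretation of results, in the paragraph after the Fig 3 caption. Three-month retention is given as 80%, so "some participants’ data are missing (service and resource use, costs, utility scores"). The only main imputation named is this: "Missing data will be imputed using the Missing not at random (MNAR) multiple imputation method", with a literature reference.

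Candidate characteristics are those the team believes affected follow-up, for example "socioeconomic status; level of pain and level of catastrophizing at the ED visit". These "will be examined to identify if they are indeed predictors of loss to follow-up". Then: "Characteristics shown to influence follow-up will be used within multiple imputations and within sensitivity analyses regarding these variables".

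Later in the paragraph, the first of three scenarios in the probabilistic sensitivity analyses sets extreme values by arm. Control patients with missing follow-up "will have utility scores at 3 months corresponding to those of the 95th percentile", and missing intervention patients take the 5th percentile. The Discussion mentions multiple imputation as the mitigation for loss to follow-up and names no mechanism.

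**The concern.** MNAR is an assumption about values nobody observed; it is not a method. To impute under it, the analyst must make imputed values differ, by a chosen amount, from those of observed patients with the same covariates. The steps in the article do not do this. They condition on observed characteristics associated with missingness, which is how imputation under MAR is carried out.

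So either the label is wrong and the analysis will be MAR, or the main result carries a departure that the trial data cannot estimate. A reader of the eventual ICER could not tell which. In the second case, no MAR reference is stated against which the extreme-value scenario could be read.

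A related weakness is the entry criterion. A variable earns its place in an imputation model mainly by predicting the values to be imputed. The stated criterion is association with loss to follow-up; association with cost or utility is not mentioned.

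**Working it through.** **Inputs.** n = 78 (Data collection). Three-month retention 80% (Data analysis and interpretation of results). Utilities measured at 0, 1 and 3 months and combined by area under the curve (Study outcomes). Alpha for the dropout screen, loss by arm, arm sizes and any MNAR shift are not stated; the values used below are assumptions.

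**1. Number lost.** 78 × 0.80 = 62.4 retained and 78 × 0.20 = 15.6 lost. In whole patients, 62/78 = 79.5% and 63/78 = 80.8%. Only 62 rounds to 80%, so 16 were lost.

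**2. Do the described steps give an MNAR analysis?** A large simulation (400,000 records, assumed parameters) used one observed baseline predictor x, utility y = 0.75 + 0.06x + error with SD 0.14, and 20% dropout. Missing y was imputed by regression on x.

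| Dropout depends on | True mean | Completers only | After imputing on x |
|---|---|---|---|
| x only (MAR) | 0.750 | 0.758 | 0.750 |
| x and y (MNAR) | 0.750 | 0.775 | 0.767 |

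Conditioning on the dropout predictor removes the bias when dropout is MAR and leaves 0.767 − 0.750 = 0.017 when it is not. Without an added departure, the described steps do not address MNAR.

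**3. How well can 16 dropouts identify predictors?** For a two-sample t-test with 16 against 62, the standard error of a standardised difference is √(1/16 + 1/62) = 0.280. At an assumed two-sided alpha of 0.05, the noncentral t gives:

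| Standardised difference | Power |
|---|---|
| 0.3 | 18% |
| 0.5 | 42% |
| 0.8 | 80% |

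The difference detectable with 80% power is about (1.96 + 0.84) × 0.280 = 0.79. With three unrelated candidates, the chance of at least one false inclusion is 1 − 0.95³ = 14%.

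**4. What would an unstated shift do?** By the trapezoid rule, the QALY weight of 3-month utility is (2/12)/2 = 0.0833, and that of 1-month utility is (1/12)/2 + (2/12)/2 = 0.125. Assume 20% missing in each arm and a shift delta applied in one arm only. That arm's mean 3-month utility moves by 0.2 × delta. The incremental QALY moves by 0.2 × delta × 0.0833, or by 0.2 × delta × (0.0833 + 0.125) if 1-month utility is also missing and shifted.

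| Delta | Mean 3-month utility | Incremental QALY, 3-month only | Incremental QALY, 1- and 3-month |
|---|---|---|---|
| 0.05 | 0.01 | 0.0008 | 0.0021 |
| 0.10 | 0.02 | 0.0017 | 0.0042 |
| 0.20 | 0.04 | 0.0033 | 0.0083 |

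The shifts double if the arms move by the same amount in opposite directions.

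**5. How many predictors can the data carry?** Assuming equal arms and equal retention, 62/2 = 31 patients per arm have 3-month data. Ten slopes fitted separately by arm leave 31/10, about 3 patients per slope. Four slopes by arm leave 31/4, about 8. Five slopes in a pooled model, one of them for arm, leave 62/5, about 12.

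**The case against.** The strongest reply is that MNAR imputation also conditions on observed covariates, so the described steps are compatible with it once a departure is added. The cited reference or a full analysis plan may give that departure. This is fair: the absence of a shift parameter from a journal article is not the finding. What stands is that the text names one assumption and describes the working of another. If a departure does exist elsewhere, the main ICER then rests on it.

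Several stronger readings are tempting, and the article does not support them:

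- **Only dropout predictors enter the model.** The text says such characteristics will be used. It does not say that only they will be, and its list is given as examples. It does not state that arm, baseline utility or 1-month outcomes are excluded.
- **A significance screen is fixed.** The text says characteristics will be examined, with no test or alpha. The p < .05 in that paragraph belongs to the subgroup analyses. Candidates are also preselected on belief, which softens the objection to a low-power screen.
- **No MNAR sensitivity analysis is planned.** The 95th/5th percentile scenario is one, and it is arm-specific. It covers 3-month utility only, and it sits among the probabilistic sensitivity analyses, which the text ties to the Objective 3 model.
- **A fifth of all costs is imputed.** ED-visit costs are derived for each participant (Study outcomes), so the gap concerns follow-up costs.
- **The two-year ICER rests on this imputation.** The physiotherapist-alone model and all 3–24 month inputs come from the literature. Objective 1 concerns the ED visit only and is unaffected.
- **The ICER is shown to change materially.** No expected incremental QALY is given, so the shifts above cannot be turned into an effect on the ICER.

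**Conclusion.** The point holds as a mismatch between label and procedure, with a weak entry criterion beside it. The declared mechanism is MNAR and the described steps are MAR-type. They amount to MNAR only with a departure that this article does not give, which would make the Objective 2 ICER and the 0–3 month trial inputs to Objective 3 depend on a value the data cannot inform.

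The loss of about 16 patients follows from the article's own figures. The 42% power at a standardised difference of 0.5 rests on an assumed 0.05 t-test. The 0.0017 to 0.0042 QALY shift rests on an assumed delta of 0.10 in one arm and 20% loss per arm. Severity: should-fix.

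**What to change.** **Main analysis.** State it as multiple imputation under MAR. Prespecify a compact predictor set that includes arm, baseline utility, ED-visit pain, and 1-month utility and cost where available, chosen for their relation to the outcomes. Do not make entry depend on a dropout screen; an examination of dropout predictors can still be reported descriptively. Impute separately by arm only if the arm sizes support that number of predictors; otherwise impute in one model with arm included.

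**Sensitivity analysis.** Keep MNAR here. Retain the existing 95th/5th percentile utility scenario as the extreme case and apply it to Objective 2 as well. Add stated, graded shifts by arm for missing utilities and stated multipliers for missing follow-up costs, so that readers can see how far the MAR assumption must fail before the conclusion changes.

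**Cost.** A few sentences and a little programming. The variables named were already collected in the trial.

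### The one specified missing-data stress scenario is a single extreme point against the intervention, changes 3-month utility but not missing costs, and as written is attached to Objective 3 and not to Objective 2

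*Protocol article*

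**What the plan says.** All references are to the protocol article.

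- **Extent of missing data.** Data analysis and interpretation of results states: "As the 3-month retention rate for the pilot pragmatic trial was 80" per cent, so that "some participants’ data are missing (service and resource use, costs, utility scores"). Data collection gives the trial size: "from September 2018 to March 2019 (n = 78").
- **Base case.** "Missing data will be imputed using the Missing not at random (MNAR) multiple imputation method". In addition, "Characteristics shown to influence follow-up will be used within multiple imputations and within sensitivity analyses regarding these variables". The content of those sensitivity analyses is not described.
- **Uncertainty.** Objective 2 is assigned non-parametric bootstrap. Objective 3 is assigned a probabilistic sensitivity analysis by Monte Carlo simulation. The next sentence reads: "Three scenarios will be considered in the probabilistic sensitivity analyses".
- **The scenario.** "The first will assume that all participants with missing follow-up data in the control group will have utility scores at 3 months corresponding" to the 95th percentile, "while all those missing in the intervention group will have scores corresponding to those of the 5th percentile". The second scenario excludes outliers. The third redefines the Markov states by pain interference instead of pain level. Neither concerns dropout.
- **Outcome.** Study outcomes bases effectiveness on area under the utility curve, with scores at baseline, 1 and 3 months, converted to QALYs and combined with costs in an ICER. The 3- to 24-month values come from the literature.
- **General promise.** The Discussion names missing follow-up data as a limitation and promises sensitivity analyses for robustness, without content.

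**The concern.** A missing-data sensitivity analysis should show how far the dropouts would have to depart from the base-case assumption before the conclusion changes. A single extreme setting cannot show this. If a favourable result fails, the reader does not know whether a small or an implausibly large departure was needed. If the base case is unfavourable to the physiotherapist model, the scenario pushes further the same way and tests nothing.

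Two further features matter for an ICER. Costs and resource use are missing for the same patients as utility, yet the scenario varies only utility. And the missing data are trial data, which drive Objective 2 directly, while the scenario is listed under the Objective 3 method. This is not detail left to a fuller document: the article lists the scenarios and fixes their values.

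**Working it through.** The article states no figure to reproduce, so the check is how far the scenario moves the result.

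**Inputs from the article:** 78 patients, two arms, 80% retention at 3 months (0.2 × 78 = 15.6, about 16 missing), visits at 0, 1 and 3 months.

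**Assumptions:** 39 per arm; 20% missing in each arm (only the overall rate is given); equal SDs; roughly normal utilities; 1-month scores kept, since the scenario sets only the 3-month score; before the change, dropouts resemble completers of their arm. Utility SD is not given, so results are in SD units.

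**Step 1. Shift in the 3-month utility difference.** With z(0.95) = 1.645:

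0.2 × (1.645 + 1.645) = 0.658 SD against the intervention.

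Skewed (beta) distributions with means near 0.8 give 0.63 to 0.65 SD.

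**Step 2. Shift in QALYs.** Trapezoids over 0–1 and 1–3 months give weights in years of 1/24 (baseline), 3/24 (1 month) and 2/24 (3 months). The 3-month score therefore has weight 1/12:

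0.658 / 12 = 0.055 SD-years.

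For an assumed utility SD of 0.10 to 0.25 this is 0.0055 to 0.0137 QALY.

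**Step 3. In standard errors.** With between-visit correlation ρ, the variance of an individual's area under the curve is (1 + 9 + 4 + 2ρ(3 + 2 + 6))/576 = (14 + 22ρ)/576 SD².

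| ρ | SD of area | SE, × √(2/39) = 0.2265 | 0.0548 / SE |
|---|---|---|---|
| 0.3 | 0.189 | 0.0428 | 1.28 |
| 0.7 | 0.226 | 0.0512 | 1.07 |

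So the shift is about 1.1 to 1.3 SE. If baseline is subtracted, the weights become −5/24, 3/24 and 2/24, the variance is (38 − 38ρ)/576, and the range is 1.1 to 1.7 SE.

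**Step 4. Break-even advantage.** Take a constant utility advantage d at 1 and 3 months. The article does not say whether the percentiles are arm-specific or common.

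- Arm-specific: d = 0.0548 / (1/8 + 1/12) = 0.26 SD.
- Common: d = 0.0548 / (1/8 + 0.8/12) = 0.29 SD.

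With 10% missing per arm the break-even is 0.13 to 0.14 SD; with 30% it is 0.39 to 0.45 SD.

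**Step 5. What the scenario can and cannot show.** On the 3-month difference, with common percentiles:

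| Observed | Stated scenario | Mirror image |
|---|---|---|
| +0.3 SD | 0.8 × 0.3 − 0.658 = −0.42 | 0.24 + 0.658 = +0.90 |
| −0.3 SD | −0.24 − 0.658 = −0.90 | −0.24 + 0.658 = +0.42 |

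A graded analysis of the +0.3 SD case would show something that neither extreme does. With control dropouts at the control mean, intervention dropouts would have to average 0.8 × 0.3 / 0.2 = 1.2 SD below that mean to remove the 3-month difference.

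**The case against.** A one-sided bound against the new model of care is a recognised conservative check, and a favourable result that survives it is strong evidence. This stands, and is why the scenario should be kept.

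The plan also has more on missing data than this scenario: an imputation labelled MNAR that covers costs as well as utility, and sensitivity analyses on predictors of dropout. Neither is restricted to Objective 3. This stands too. The scenario is the only *specified* stress test, not the only missing-data provision, and it would be wrong to say that missing costs go wholly unexamined.

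Three stronger readings are tempting, and the article does not support them.

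- *That the scenario overturns almost any result.* On the 3-month utility difference alone, 0.658 / 0.2265 = 2.9 SE. But the outcome is area-under-the-curve QALYs with costs, where the shift is less than half of that under the Step 3 assumptions without baseline subtraction. Unfavourable results are reinforced, not overturned. In Objective 3 the later values come from the literature and the base-case Markov states rest on pain level, so the effect on the two-year ICER cannot be derived from the article.
- *That it shows nothing about robustness.* Surviving it does show something; only failing it is uninformative.
- *That fixed values shrink the variance.* Variation among dropouts disappears, but arm variance rises: 0.8 + 0.16 × 1.645² = 1.23 SD².

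Finally, the placement under Objective 3 is read from adjacent sentences. If Objective 2 was also intended, one clause would settle it.

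**Conclusion.** The concern holds in a limited form. The one specified stress scenario is extreme, runs one way, varies 3-month utility only and, as written, is not applied to the trial-based cost-utility analysis. Under the stated assumptions it is a moderate displacement of the QALY difference, about 0.055 SD-years or 1.1 to 1.3 SE. That is enough to reverse a constant advantage below about 0.26 to 0.29 SD. If 1-month scores were also set to the percentiles, the break-even would rise to 0.66 to 0.82 SD, but the article sets only the 3-month score. The size depends on the assumed equal split and dropout, equal SDs, the correlation range and dropouts otherwise resembling completers. The structural points (no mirror, no gradation, no cost counterpart, no stated scenario for Objective 2) do not depend on these assumptions. This is a worthwhile, inexpensive improvement to an existing check, not a flaw that invalidates the analysis.

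**What to change.** 1. Keep the 95th/5th percentile scenario as an outer bound, add its mirror image, and say which distribution the percentiles come from.
2. State that both apply to Objective 2 and are carried into Objective 3.
3. Add a small graded (delta or tipping-point) analysis for Objective 2, carried into Objective 3. Shift imputed utilities up and down, and scale imputed costs up and down, separately by arm. Fix the steps before the analysis.
4. Report where incremental net benefit changes sign, for the Health system and Societal perspectives, so that readers can judge whether that departure is plausible.

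No new data are needed. The cost is extra analysis runs and more output. Two arms, two quantities and two perspectives multiply quickly, so the grid should be kept coarse for a 78-patient pilot.
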